## Abstract

**Trial Registration:**

The trial began recruiting in May 2024 (Trial Registry: NCT06111651, Version 5, June 13, 2024). Participants are expected to complete their 3‐month follow‐up assessments at the end of fall 2025.

## Introduction

1

Minoritized children are at a heightened risk for various emotional problems (e.g., anxiety, depression, and psychological distress) and physical health issues (e.g., obesity) due to the known impact of individual and structural racism (Berry et al. 2021). Structural racism manifests in unequal access to high‐quality education, safe housing, healthy foods, and medical care, while individual‐level (or interpersonal) racism includes daily experiences of discrimination and bias—all of which have been linked to chronic stress, poor emotion regulation, and biological dysregulation in children (Williams et al. 2019). Black and Latiné children are disproportionately exposed to both forms of racism, which may help explain why they consistently experience the highest rates of many health problems (Berry et al. 2021). For example, Black and Latiné children have twice the rates of obesity as compared to their white counterparts From Crisis to Opportunity 2021). Black children between the ages of 3 and 17 also have 50% higher rates of behavior/conduct problems as compared to non‐Latiné White children (Bitsko et al. 2022). This mounting evidence has fueled recent calls to address health disparities by directly targeting the effects of racism in child health outcomes through culturally responsive interventions (Gordon 2020).

Family‐based preventive intervention is a promising strategy for preventing child health problems including social‐emotional problems (Menting et al. 2013; Sanders et al. 2014) and unhealthy lifestyle behaviors (e.g., sleep problems, sedentary behavior) (Soltero et al. 2021). However, preventive interventions focused on either or both of the aforementioned health domains have rarely included content to promote ethnic‐racial socialization, a potentially powerful protective factor for minoritized children. Ethnic‐racial socialization relates to how families teach their children about the values, traditions, and practices associated with their ethnic‐racial group and may play a key role in mitigating the negative effects of racism on health outcomes (Brody et al. 2021; Neblett et al. 2008) and in contributing to children's social‐emotional functioning (Umaña‐Taylor and Hill 2020) and healthy lifestyle behaviors (Conway et al. 2021; Granberg et al. 2009; Wang et al. 2021). The omission of ethnic‐racial socialization strategies from preventive parenting interventions is a crucial gap that may be limiting engagement, reach, and impact with minoritized families. Therefore, the main objective of the proposed project is to examine whether providing parenting support, with an added emphasis on ethnic‐racial socialization, improves social‐emotional functioning and healthy lifestyle behaviors in young Black and Latiné children.

### Limitations of Existing Parenting Interventions for Supporting Child Health

1.1

Positive parenting practices, such as parental monitoring, positive reinforcement, and limit setting, are associated with greater child social‐emotional health (Leijten et al. 2019) and healthy lifestyle behaviors (Soltero et al. 2021). As such, many of the most effective child health‐promoting interventions teach positive parenting practices (Ling et al. 2017; Ochoa and Berge 2017; Smith et al. 2017). A key limitation of family‐based prevention efforts is that they have failed to incorporate ethnic‐racial socialization, a critical contributor to child health and well‐being. Two of the most effective ethnic‐racial socialization strategies parents can use are: (a) fostering racial‐ethnic pride and (b) preparing children to handle discrimination (Umaña‐Taylor and Hill 2020). However, these strategies have been largely left out of parenting interventions for minoritized groups. In fact, only 1 of the 36 evidence‐based family‐focused interventions listed on the Blueprints registry (Blueprints for Healthy Youth Development—Committed to Healthy Youth, Families and Communities n.d.) included content on ethnic‐racial socialization. This is a critical gap because positive ethnic‐racial socialization is linked to improved child psychosocial functioning and can protect against the harmful effects of racism (Brody et al. 2021). For example, a recent meta‐analysis found that increasing ethnic pride, one ethnic‐racial socialization strategy, was a robust predictor of positive child outcomes, including ethnic‐racial identity, self‐esteem, academic achievement, adaptive coping, and psychological well‐being (Umaña‐Taylor and Hill 2020). Although few studies have examined the link between ethnic‐racial socialization and child physical health, there is evidence that promoting ethnic‐racial socialization can buffer the negative effects of racism (Neblett et al. 2008, 2012). This is important because experiencing racism is shown to negatively impact physical health outcomes, such as increasing cortisol levels, body weight, and sleep problems (Cave et al. 2020). Therefore, incorporating ethnic‐racial socialization has the potential to enhance the efficacy of family‐based interventions for child health outcomes while trying to offset the effects of racism.

Another limitation in the field of family‐based prevention is that most studies have focused on addressing social‐emotional functioning and healthy lifestyle behaviors separately, rather than adopting a more holistic approach by integrating the two domains into a unified intervention. Addressing these two domains in separate interventions is likely more cumbersome for providers and participants and misses out on the potential interactive effects of targeting both domains in the same intervention. Multiple studies have found that parenting interventions aimed at decreasing disruptive behavior also had positive effects on child lifestyle behaviors, such as physical activity and sedentary behavior, highlighting the potential for cross‐over effects of parenting interventions (Brotman et al. 2012; Smith et al. 2015). Meta‐analytic findings suggest that interventions aimed at increasing children's healthy lifestyle behaviors (e.g., sleep, sedentary behavior, physical activity) were particularly effective when including parenting support (Ling et al. 2017). However, none of these studies involved a purposeful integration of evidence‐based practices to jointly support child physical and emotional health. Thus, there is a need for integrated family‐based interventions aimed at the dual promotion of child social‐emotional and physical health, as they may offer a more efficient, sustainable approach to prevention (Hurley et al. 2016).

Despite increasing interest in family‐based interventions to improve child health, there are two additional limitations in the literature that the current study seeks to address: most interventions have focused on (a) late childhood and adolescence (e.g., Migueles et al. 2019) or (b) youth who have already experienced problematic health outcomes (e.g., Menting et al. 2013). For example, four of the largest obesity prevention trials conducted in the United States, including COPTR (Pratt et al. 2013), GEMS (Obarzanek and Pratt 2003), TAAG (Webber et al. 2008), and Pathways (Caballero et al. 2003), focused on 7‐ to 13‐year olds. In terms of prevention scope, many of these efforts have utilized indicated prevention, which refers to programs designed specifically for individuals who already exhibit early signs of problems or elevated risk profiles (Muñoz et al. 1996). A recent review of parenting programs for reducing child disruptive behavior found that the vast majority involved indicated prevention, with only 8 of the 154 trials adopting a universal prevention perspective (Leijten et al. 2019). This imbalance presents a significant missed opportunity. Universal interventions are delivered to broad populations, regardless of individual risk, and are particularly well‐suited for public health promotion, as they reach children before symptoms emerge and can help shift population‐level outcomes (Matthay et al. 2021). Moreover, early childhood is a sensitive period for physical and psychosocial development (Dunn et al. 2019; Tierney and Nelson 2009). Implementing universal prevention efforts during this developmental window may lay a stronger foundation for long‐term health and well‐being and prevent future problematic trajectories.

### Hybrid Effectiveness‐Implementation Studies

1.2

To continue to improve the delivery and reach of evidence‐based solutions for child health promotion, implementation science has emerged (Bauer et al. 2015). Implementation science seeks to accelerate the translation of evidence‐based practices into usual care (Bauer et al. 2015). This is particularly important in low‐resource settings, for which evidence‐based practices are often less feasible and effective (Chu and Weiser 2021). One promising strategy for accelerating the spread of evidence‐based practices is the type 1 hybrid effectiveness‐implementation approach, which simultaneously tests (a) intervention effectiveness and (b) its potential for widespread dissemination (Curran et al. 2022). This is often done by gathering implementation outcomes—such as providers' opinions on intervention acceptability, feasibility, and delivery cost—alongside the evaluation of intervention outcomes (Studts et al. 2022). Assessing implementation outcomes simultaneously can help create implementation strategies to address barriers to intervention delivery and improve the reach, impact, and sustainability of evidence‐based practices for minoritized children (Proctor et al. 2011).

### Current Study Aims

1.3

The proposed study involves the development and preliminary evaluation of an integrated family‐based intervention (hereafter referred to as the ROOTS program) to promote the social‐emotional functioning and healthy lifestyle behaviors of Black and Latiné children ages 3–6. This hybrid effectiveness‐implementation study has the following aims: examine various implementation outcomes, such as the feasibility and acceptability of recruitment, retention, and fidelity, as well as potential barriers and facilitators to intervention delivery (Aim 1) and evaluate the pre‐post changes in child and parent outcomes as compared to an active control condition (Aim 2). If successful, this study can provide justification for larger efficacy trials that could ultimately lead to the availability of more holistic integrated interventions for promoting the health and well‐being of Black and Latiné children.

## Methods

2

### Study Setting and Design

2.1

Because the protocol will be implemented virtually, families living anywhere in the state of South Carolina will be able to participate. To pilot the feasibility of the ROOTS program, the study will use a longitudinal two‐arm randomized control trial design in which families are randomized into a parenting intervention (*n* = 30) or a control (*n* = 30) condition on a 1:1 ratio. We selected a nutrition control condition that is a similar length (6 weeks) and provides a similar structure (offers parents new strategies and a workbook to reflect on their progress and goals). This decision was based on empirical evidence suggesting a need for alternative approaches to intervention research to maximize participant engagement and minimize ethical concerns related to withholding services from underserved populations (Henry et al. 2017). Assessments will occur at three timepoints: pre‐intervention (T1), post‐intervention (T2), and 3‐month follow‐up (T3). After completing the third assessment, each condition will have the opportunity to receive the materials from the other condition.

The hybrid effectiveness‐implementation approach adopted for this study examines intervention outcomes while concurrently assessing barriers and facilitators related to successful program delivery (see Figure 1). Blinding will occur at several levels, primarily with participants, outcome assessors, and data analysts. For example, intervention participants will not be aware of which intervention group is considered the treatment or control; rather, they will be instructed that the study seeks to compare the effects of two health interventions. Outcome assessment will be conducted using Qualtrics, which prevents potential bias from using unblinded assessors. Blinding will also occur at the data analyst level, specifically related to assessing outcomes.

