#### Program Format and Delivery

2.4.3

ROOTS consists of 6 weekly one‐on‐one sessions, each lasting approximately 60–90 min. Sessions follow a structured format that includes a review of homework activities, didactic teaching, interactive discussions, and role play. Parents meet virtually via Zoom in either English or Spanish, depending on their preference. Sessions are led by trained interventionists who match the racial and ethnic backgrounds of participants. Parents receive a ROOTS toolkit by mail, which includes a workbook, culturally relevant children's books to support ethnic‐racial socialization, a program schedule, and study‐branded materials (e.g., handheld fan, hand sanitizer). Participants also receive weekly text message reminders about homework and appointment dates.

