#### Nutrition Control Condition

2.4.5

Parents in the active control condition will receive a six‐session self‐directed nutrition intervention based on best practices for healthy eating. These materials were compiled from Myplate.gov and Nibbles for Health and cover a range of topics, including nutrition basics, trying new foods, breakfast and snacks, fruits and vegetables, protein and dairy, and bread and grains. Parents are given a workbook that includes empty spaces for goal setting and behavior tracking, as well as a study overview schedule and study swag. After the 3‐month follow‐up assessment (T3), parents in the nutrition control condition will receive the parenting intervention materials and have the option to attend a 1‐h consultation session to provide an overview of the materials.

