Characteristics of individuals	Whether parents and providers view the intervention as valuable and relevant to families	●	●	Participants' and interventionists' perceptions of the acceptability and appropriateness of ROOTS for Black and Latiné families (acceptability of intervention measure; intervention appropriateness measure; interview questions on parents' engagement with ROOTS materials)
Implementation process	How implementing the intervention impacts current operating procedures and whose buy‐in, input, and expertise is needed to deliver and sustain the intervention	●	●	Qualitative and quantitative assessments with interventionists about perceived barriers and facilitators to intervention delivery, such as ease of implementation, costs, perception of community buy‐in (e.g., Feasibility of implementation measure)

*Note:* Qual = qualitative measure. Quant = quantitative measure. Some overlap exists between domains in the RE‐AIM and CFIR frameworks. For instance, RE‐AIM's *adoption* and *maintenance* dimensions align with CFIR's *inner setting* and *characteristics of individual* domains, as they reflect organizational readiness and individual perspectives. As a result, several measures correspond to more than one framework domain and are listed in multiple sections of the table to reflect this integration.

**Table 3 jmft70052-tbl-0003:** Main and secondary outcome measures at T1, T2, and T3.

Construct	Measure	Reporter	Description
Main child outcomes			
Social‐emotional functioning	***** *SDQ* (Goodman 1997)	Parent	25 items assessing emotional symptoms, peer problems, conduct problems, hyperactivity, and prosocial behaviors *α* = 0.88 (Palmieri and Smith 2007)
Sleep	Axivity	Objective measure	Average nightly sleep duration and quality over a 7‐day period (Martin and Hakim 2011)
	^ **+** ^ *PCSIS* (Alfano et al. 2013)	Parent	12 items assessing sleep‐related parenting behaviors and interactions, such as sleep dependence, sleep conflict, *α* = 0.82
Physical activity	Axivity	Objective measure	Accelerometer‐derived physical activity intensity (e.g., light, moderate) over a 7‐day period (Lynch et al. 2019)
Sedentary behavior/screen time	Axivity	Objective measure	Accelerometer‐derived sedentary time over a 7‐day period (Lynch et al. 2019)
Secondary parenting outcomes			

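### Blinded outcome assessment is claimed, but on all six questionnaires the rater is a parent who knows the programme received, and only ROOTS includes live coaching, which the description of the control does not mention

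*Protocol article*

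**What the plan says.** Section 2.1 (Study Setting and Design) of the protocol article makes a general claim: "Blinding will occur at several levels, primarily with participants, outcome assessors, and data analysts". It then gives the content for each level.

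- **Participants:** "intervention participants will not be aware of which intervention group is considered the treatment or control". They are told that two health interventions are being compared.
- **Outcome assessors:** "Outcome assessment will be conducted using Qualtrics, which prevents potential bias from using unblinded assessors".
- **Analysts:** blinded when assessing outcomes.

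The same section justifies the control as lasting a similar time (6 weeks) and says that it "provides a similar structure (offers parents new strategies and a workbook to reflect on their progress and goals").

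Delivery is described later. In Section 2.4.3, ROOTS is six weekly one-on-one Zoom sessions, "each lasting approximately 60–90 min". "Sessions are led by trained interventionists who match the racial and ethnic backgrounds of participants". In Section 2.4.5, the control is a six-session self-"directed nutrition intervention based on best practices for healthy eating". The only live contact described there is an optional one-hour consultation after T3, the 3-month follow-up.

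Table 3 lists the parent as reporter for every questionnaire. One of these is the SDQ, described as "25 items assessing emotional symptoms, peer problems, conduct problems, hyperactivity, and prosocial behaviors". The accelerometer is the only other source of outcome data.

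**The concern.** Blinding an outcome assessor means that whoever assigns the score does not know the allocation. On a parent-report scale that person is the parent. Having the parent fill in the form on a survey platform keeps a staff interviewer out of the process. It does not change what the parent knows. The stated safeguard therefore does not deliver the stated property for the questionnaires.

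The contact difference adds to this. Parents in one arm spend weeks with a coach working on parenting, socialization and routines, and then rate those same areas. Parents in the other arm work alone through nutrition material. A difference on a parent-rated scale could reflect programme content, the attention received, or what the parent expects to have changed.

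The interpretation of Aim 2 is at stake. Section 2.8 puts the emphasis on effect sizes and 95% confidence intervals, and Section 1.3 says a successful study could justify larger efficacy trials. A reader told that assessment was blinded and the control similarly structured would give the questionnaire effects more weight than the design supports.

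**Working it through.** The plan states no figure for blinding or bias, so there is nothing of its own to reproduce. The check is a count, a contact-time calculation and a labelled illustration.

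**1. Who rates what (Table 3).**

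| Group | Parent-rated | Device-measured |
|---|---|---|
| Main child outcomes | SDQ, PCSIS | sleep, physical activity, sedentary time |
| Secondary parenting outcomes | CSAB, RaSCS, PSAS, Parenting Scale | none |

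Parent-rated questionnaires: 2 + 4 = 6 of 6. The SDQ is the only measure of social-emotional functioning. All four secondary scales are parent-rated.

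**2. What the parent knows.** The parent has either attended live parenting sessions or been given a nutrition workbook, so the programme received is known. Section 2.1 withholds only the treatment/control label. That is masking to the label, not to the intervention.

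**3. Coach contact before T3.**

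- ROOTS: 6 × 60 min / 60 = 6 h, up to 6 × 90 min / 60 = 9 h per family at full attendance.
- Control: 0 h of coach sessions. The optional consultation comes after T3.
- Both arms: Section 2.6 gives each participant a point person available by text and does not restrict reminders to one arm. The zero therefore refers to coaching, not to all staff contact.

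**4. What each outcome type is exposed to.**

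| Outcome type | Rater knows programme | Coach-contact difference |
|---|---|---|
| Six questionnaires | yes | yes |
| Accelerometer outcomes | no human rater | yes |

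**5. Illustration only.** The shift below is an assumption; the documents offer none. With 30 per arm and no covariate adjustment or dropout, the standard error of a standardized difference is √(2/30) = 0.258, and the 95% interval half-width is 1.96 × 0.258 = 0.51 SD. If the true effect is zero and reporting or attention shifts the difference by b, the chance that the interval lies wholly on the ROOTS side is 1 − Φ(1.96 − b/0.258).

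| Assumed b (SD) | Chance |
|---|---|
| 0 | 2.5% |
| 0.1 | 5.8% |
| 0.2 | 11.8% |
| 0.3 | 21.2% |

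This shows sensitivity. It is not an estimate of bias in this trial.

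**The case against.** The strongest reply is that the assessor sentence is narrower than it looks. It concerns staff assessors who know the allocation, and self-completed online forms do close that route. Parents are also told only that two health programmes are being compared, which may dampen expectancy. Both points are fair. Neither makes the person scoring the SDQ unaware of the programme received, and the list of blinded parties still names outcome assessors without qualification.

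A second reply is that the control is legitimate. Section 2.1 gives engagement and the ethics of withholding services as reasons, the protocol calls it an active control and never an attention control, and coach contact is part of the ROOTS package. That stands: the choice of comparator is not the fault. A reader might infer that the similar-structure statement is false. It is not, because the features it lists are true. It is incomplete, since it omits delivery mode and contact time.

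A reader might also infer that parents are simply unblinded, or that programme branding lets them work out which arm is under test. The documents do not support either. Masking to the label is stated, and nothing shows how the study is named to parents. Control families also receive study-branded items.

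Finally, three of the four main child constructs (sleep, physical activity, sedentary behavior) have device measures, and Aim 2 is described as preliminary. This limits the reach of the point but does not remove it.

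**Conclusion.** The concern holds in this form. For all six questionnaires, outcome assessment is not blinded in the sense Section 2.1 conveys, because the rater is a parent who knows the programme received and is masked only to the label. The control matches ROOTS on duration, new strategies and a workbook, but not on coach contact: 6–9 hours at full attendance against none before T3. Parent-reported effects therefore cannot be separated from expectancy and attention. Device-measured effects are free of reporter bias but still carry the contact difference.

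It would go too far to say that the questionnaire effects are biased by a known amount, or that a later trial will be mis-sized because of them. The size of any bias cannot be derived from the documents, and the protocol does not say that it will size a trial from the SDQ. The progression criteria in Section 2.5.1 concern recruitment, enrollment, session completion and assessment completion, so Aim 1 is unaffected. This is a matter of correct description and interpretation, not redesign.

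**What to change.** 1. In Section 2.1, replace the Qualtrics sentence and the list of blinded parties with text to this effect: *parents are masked to the treatment/control label only; parent-reported outcomes are rated by a parent aware of the programme received; analysts are blinded.*
2. Where the control is described (Sections 2.1 and 2.4.5), state that ROOTS includes six live one-on-one sessions totalling 6–9 hours, that the control has no coach sessions before T3, and that text support and reminders are not limited to one arm.
3. Report and interpret device-measured and parent-reported effects separately. Attribute no effect of either kind to programme content apart from coach contact.
4. Optionally, add an item at T3 asking which programme the parent believes is being tested. Recruitment began in May 2024 and T3 assessments were expected to finish at the end of fall 2025, so this is useful only if assessments are still open.

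Items 1 to 3 change wording and the layout of results only. The cost is a less favourable account of blinding.
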